Recently a new opioid, remifentanil, was introduced. Remifentanil, is a new synthetic opioid (anilidopiperidine) with direct agonist action specifically on µ-opioid receptors (6). The rapid onset and offset of the drug make remifentanil very suitable for administration via patient controlled analgesia (PCA), which can be used for analgesia during labor. Placental transfer of remifentanil does occur but appears to be rapidly metabolized, redistributed, or both. There were no adverse neonatal or maternal effects, only mild maternal sedation and respiratory changes (7). There have been multiple clinical studies on the use of remifentanil in the parturient (8-20).

A recent randomized study that compared RPCA with EA showed that in terms of pain scores (pain-intensity), EA is superior to that provided by RPCA. However, there was no difference in the pain appreciation scores between the treatments (21).

These findings were confirmed in our own pilot study that compared pain and pain appreciation scores in 20 women, randomized for RPCA or EA.

In our unpublished data (pilot study and STER study), 100 women received RPCA and only in one case medication had to be stopped because of serious side-effects (decrease in respiratory rate).

We hypothesize that RPCA is as effective in improving pain appreciation scores as EA, with lower costs and easier achievement of 24 hours availability of pain relief for women in labor.

Since we know from other studies that equality in pain appreciation scores can be anticipated, this study will, next to pain appreciation, also investigate patient satisfaction and costs. In this study patients receiving PCA remifentanil will titrate themselves to an acceptable level of pain relief by pressing a button (and receiving an analgesic bolus dose).

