## Dosages, dosage modifications and method of administration

Remifentanil patient controlled analgesia, intravenous administration; 30 microgram boluses, lockout time 3 minutes, maximum dose limit 1200 microgram/hour. It is possible to increase the bolus dosage to 40 microgram in case of insufficient pain relief, or to decrease the dose to 20 microgram in case of signs of respiratory depression or sedation.

Epidural analgesia, epidural administration according to local protocol. Suggested protocol: loading dose of 25 mg (12.5 ml ropivacaine 0.2%), continuous infusion of ropivacaine 0,1% plus sufentanil 0,5 microgram/mL.

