### Secondary study parameters/endpoints

If RPCA is equivalent to EA with respect to pain appreciation the next endpoint will be the costs of both interventions. For both strategies the cost of perinatal care for mother and child, starting at the onset of labor and ending ten days after delivery, will be registered and compared (without discounting). The costs consist of costs of delivery/childbirth (course and mode of delivery), postnatal maternal care (hospitalization, outpatient visits), neonatal care (admission to NICU/neonatology ward, outpatient visits) and primary care (midwife, general practitioner, maternity care).

Maternal outcome

- Morbidity (post spinal headache, postpartum haemorrhage (>1 litre or administration of blood products), uterine rupture, eclampsia, amniotic fluid embolism, myocardial infarction, admission to ICU, other (defined as major maternal morbidity by local researchers).
- Maternal mortality
- Prolonged maternal admission. Admission in days measured from delivery of the child.
- Diagnosis during admission: endometritis, suspected infection, UTI treated with antibiotics, wound infection treated with antibiotics, obstructed bowel disease, pneumonia, trombo-embolic complications, hypertensive disorders, postpartum haemorrhage, post caesarean, pre-eclampisa/HELLP, admission due to condition child, other.

Maternal parameters

- pain scores, measured hourly from start of labor using a VAS scale
- pain appreciation scores, measured hourly from the start of labor and after start of pain relief every 15 min in the first hour and hourly after that on a VAS scale.
- satisfaction with pain, measured on a scale of 0-10 after delivery
- side effects, during administration of pain relief
  - hypotension (systolic blood pressure <90 mmHg of <25% below baseline)
  - nausea/vomiting (none, mild, moderate, severe)
  - itching (none, mild, moderate, severe)
  - respiratory depression (respiratory rate <8/min)maternal fever during labor (temperature >38°C)

Neonatal outcome

- Apgar scores ≤ 6 after 1 and 5 minutes
- Umbilical cord pH < 7.10
- Admissions to the neonatal ward

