## Study procedures

Women will be asked to participate in this study before active labor has started, preferably during antenatal consult in the third trimester. They will be randomized and allocated to one of the treatment groups. If they request pain relief during labor they will be treated according to randomization with:

1. Remifentanil patient controlled analgesia; 30 microgram boluses, lockout time 3 minutes, maximum dose limit 1200 microgram/hour. Possibility of increasing or decreasing the bolus dose. When indicated EA is available.

2. Epidural analgesia; according to local protocol. When indicated RPCA is available.

There will be no additional invasive tests performed. Maternal vital parameters (temperature, heart rate, blood pressure, respiratory rate and pulse oxymetry) will be monitored non invasively at regular intervals. In the first hour after starting pain relief these parameters will be monitored with intervals of no longer than 15 minutes, after that with intervals of no longer than 1 hour. Maternal pulse oxymetry will also be monitored continuously.

Fetal heart rate and uterine activity will be measured continuously by external monitoring. When data are difficult to interpret or complications (such as meconium stained amniotic fluid, failure to progress in labor) occur, invasive monitoring by means of scalp electrode and intra-uterine pressure recording can be instituted.

Observations for known side effects will be made; respiratory depression, hypotension, nausea/vomiting and itching. Side effects will be managed by established local protocols.

Hypotension (systolic blood pressure < 90 mmHg or > 25% below baseline) will be treated with intravenous fluids, ephedrine 5 mg i.v. or phenylephrine 0.1 mg i.v. When oxygen saturation drops below 92% oxygen will be given.

Maternal pain score and pain appreciation score will be assessed using a visual analogue scale (VAS) ranging from 0-10. Women will be asked to mark the level of pain experienced during a contraction every hour starting at admission in the delivery room. Pain appreciation scores will be asked every hour, participating women will be asked to mark their level of satisfaction with analgesia. This will also be assessed using the visual analogue scale ranging from 0-10. After delivery an overall satisfaction score with pain(0-10) will be asked. Patient satisfaction will also be assessed by HADS and WDQ.

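### Sedation is not a listed outcome in either arm, and the respiratory endpoint is a rate below 8/min at intermittent checks, with no desaturation event defined

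*Protocol*

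**What the plan says.** Maternal side effects are a secondary objective (Protocol section 2). Section 6.1.2 lists those to be compared during pain relief: hypotension, nausea/vomiting and itching (both graded), fever, and "respiratory depression (respiratory rate <8/min". No saturation, oxygen or sedation item is in that list.

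On vital signs, including respiratory rate and blood pressure, section 6.3 says: "In the first hour after starting pain relief these parameters will be monitored with intervals of no longer than 15 minutes", and "after that with intervals of no longer than 1 hour". It adds: "Maternal pulse oxymetry will also be monitored continuously". Oxygen is given when saturation falls below 92%. The side effects to be watched for are stated as: "Observations for known side effects will be made; respiratory depression, hypotension, nausea/vomiting and itching".

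The Introduction summarises earlier experience with remifentanil as "only mild maternal sedation and respiratory changes (7", and section 5.2 repeats this. Section 5.2 also names drowsiness among the reported complications of epidural analgesia. The dosage section allows the RPCA bolus to be lowered "in case of signs of respiratory depression or sedation".

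Section 8.1 lists respiratory depression (yes/no), maternal saturation (continuous), oxygen given (yes/no) and changes in RPCA bolus dose. Sedation is not listed. Section 7.2 records all adverse events that women report or staff observe, and makes respiratory failure needing ventilation a study-defined serious adverse event.

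**The concern.** The trial asks whether RPCA can be a first-choice method, so maternal respiratory safety and alertness bear directly on the decision. Two gaps stand out.

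First, the protocol treats sedation as important enough to change the dose but provides no systematic record of it in either arm.

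Second, the only named respiratory event depends on a reading that may be an hour apart after the first hour, for a drug described as having rapid onset and offset. The one respiratory signal that is followed continuously has no event attached to it. If episodes are short, many will not be counted, and the comparison of maternal side effects loses the ability to show a difference that exists.

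This is not merely a matter for a statistical analysis plan. The protocol fixes the endpoint, and sedation that was not graded at the bedside cannot be recovered at analysis.

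**Working it through.** **1. The lists side by side**

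| Item | Named as effect or trigger | 6.1.2 endpoint | 6.3 observation list | 8.1 variable |
|---|---|---|---|---|
| Rate below 8/min | yes | yes | yes (respiratory depression) | yes/no |
| Saturation below 92% | trigger for oxygen (6.3) | no | monitored continuously, not listed as a side effect | saturation as a continuous variable; no event |
| Oxygen given | consequence of the above | no | not listed as a side effect | yes/no |
| Sedation or drowsiness | remifentanil effect (1, 5.2); bolus trigger (dosage section); epidural complication (5.2) | no | no | no; bolus changes listed without a reason |

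The protocol states no figure on this point, so there is none to reproduce.

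**2. Chance that a scheduled check meets one episode**

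Inputs: check intervals of 15 and 60 minutes (section 6.3, taken at their maxima). Episode length D is an assumption, because the protocol gives none; the range shown is 2 to 30 minutes. For one episode at a random time, P = min(1, D / interval).

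| D (min) | 15-minute checks | 60-minute checks |
|---|---|---|
| 2 | 2/15 = 13% | 2/60 = 3% |
| 5 | 5/15 = 33% | 5/60 = 8% |
| 10 | 10/15 = 67% | 10/60 = 17% |
| 15 | 100% | 15/60 = 25% |
| 30 | 100% | 30/60 = 50% |

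If a woman has k independent episodes, the chance of meeting at least one rises to 1 − (1 − P)^k. The table is therefore the single-episode case.

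**3. What equal under-detection does to the comparison**

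Let s be the probability that a woman with the event is counted, the same in both arms. Observed risks are s·p1 and s·p2. The ratio is s·p1 / (s·p2) = p1/p2, unchanged. The difference is s·(p1 − p2), shrunk by the factor s.

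For power, take n = 568/2 = 284 treated women per arm (section 4.4) and a two-sided 5% test. With p1 and p2 now the observed risks and p̄ their mean:

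Power = Φ{ [ |p1 − p2| − 1.96·√(2p̄(1 − p̄)/n) ] / √[ (p1(1 − p1) + p2(1 − p2))/n ] }

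The true risks are assumptions. The only respiratory figure in the protocol is one stop for decreased respiratory rate among 100 women given RPCA (exact 95% interval 0.03% to 5.4%). That counts treatment stops, not episodes.

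| Share detected (s) | 5% v 0.5% | 10% v 1% | 20% v 2% |
|---|---|---|---|
| 100% | 90.9% | 99.7% | 100% |
| 50% | 63.5% | 90.9% | 99.7% |
| 25% | 36.8% | 63.5% | 90.9% |
| 10% | 17.4% | 30.5% | 53.9% |

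Worked line, 10% v 1% with s = 25%: observed risks are 2.5% and 0.25%, p̄ = 1.375%, and the difference is 2.25 points instead of 9. The null standard error is 0.00977 and the alternative 0.00973. Then (0.0225 − 1.96 × 0.00977)/0.00973 = 0.34 and Φ = 63.5%.

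The normal approximation is rough in the sparse cells. At s = 10% in this scenario, 284 × 0.01 = 2.8 and 284 × 0.001 = 0.3 events are expected. The ordering across rows is more reliable than the exact values.

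**The case against.** The strongest reply is that respiratory harm is not captured by the rate criterion alone. Section 8.1 already lists saturation and oxygen given. Since section 6.3 gives oxygen below 92% and the oximeter runs continuously, oxygen yes/no is close to a marker of desaturation. Calling saturation continuous states a data type; nothing says that readings will be averaged, and the summary may be left to an analysis plan. The intervals are maxima, and watching for side effects is not confined to scheduled checks. Sedation may be recorded as an observed adverse event or leave a trace in bolus changes. Severe respiratory events are serious adverse events reported to the monitoring board.

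Most of this stands, and it limits the point. It does not close the gap: oxygen given is recorded without a reason and lies outside the section 6.1.2 endpoints. Continuous monitoring is not the same as a defined, recorded event. Adverse event reporting gives no grade and no common schedule for sedation.

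A reader might infer that RPCA harms are undercounted and the safety comparison is tilted towards RPCA. The documents do not support that. The check schedule is common to both arms, and blood pressure, on which epidural hypotension depends, follows the same intervals. Drowsiness is named for epidural analgesia too. The documented RPCA risks in section 5.3 (respiratory depression, nausea/vomiting, itching) are all endpoints. Nor does it follow that sedation goes wholly unrecorded.

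**Conclusion.** The point holds as a gap in outcome definition that affects both arms. Sedation is named as an effect and a dose-change trigger but is not systematically measured. The respiratory endpoint rests on intermittent rate readings, while the continuously monitored signal has no event definition.

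The size depends on assumptions. A single episode of 2 to 30 minutes is met by an hourly check with probability 3% to 50%. With assumed true risks of 10% and 1%, power falls from 99.7% at full detection to 63.5% at 25% detection and 30.5% at 10%. These figures assume 284 treated women per arm, equal detection in both arms and no dilution from cross-over. They also assume that events count only when a check meets them, which is the pessimistic case.

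Under equal detection the relative risk is unaffected. The absolute difference shrinks, which flatters whichever arm has more events. On the protocol's own list of risks that would be RPCA for respiratory depression, but a bias towards RPCA is likely only in that sense and is not shown. The primary outcome is untouched. This is a worthwhile and inexpensive improvement, not a defect that undermines the trial.

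**What to change.** In sections 6.1.2 and 8.1 add:

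- For both arms, a desaturation event, yes/no, defined as any SpO2 below the 92% level already used in section 6.3 during pain relief. Report it separately from respiratory rate below 8/min and from oxygen given.
- For both arms, sedation graded none, mild, moderate or severe at the existing vital-sign checks, in the same form as nausea and itching. Add it to the observation list in section 6.3.
- The recorded reason for each decrease in the RPCA bolus.

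The cost is a few case report form fields and some oximetry artefact, under one definition for both arms. The oximeter already runs, the checks already take place and bolus changes are already listed. Dosing and clinical management do not change.

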### Other study parameters

Possible factors that could influence interpretation of maternal parameters during labor and neonatal outcome, also factors that could influence economical evaluation.

- Maternal status: age, race, medical history, obstetric history, parity, blood pressure, weight, information regarding labor (induction, meconium stained amniotic fluid, augmentation with oxytocin, instrumental delivery).
- Maternal medication: started before or during pregnancy, during labor.
- Condition of fetus: CTG tracing (normal, non-reassuring).

## Randomisation, blinding and treatment allocation

Randomization stratified for centre and parity will take place after informed consent. Randomization will be performed through a web-based database located in the central data collection unit in the AMC in Amsterdam. Women will be randomly allocated to receive epidural analgesia of remifentanil PCA when they request pain relief during labor. There will be no blinding, as this is not possible with these two treatment methods.

## Study procedures

Women will be asked to participate in this study before active labor has started, preferably during antenatal consult in the third trimester. They will be randomized and allocated to one of the treatment groups. If they request pain relief during labor they will be treated according to randomization with:

1. Remifentanil patient controlled analgesia; 30 microgram boluses, lockout time 3 minutes, maximum dose limit 1200 microgram/hour. Possibility of increasing or decreasing the bolus dose. When indicated EA is available.

2. Epidural analgesia; according to local protocol. When indicated RPCA is available.

There will be no additional invasive tests performed. Maternal vital parameters (temperature, heart rate, blood pressure, respiratory rate and pulse oxymetry) will be monitored non invasively at regular intervals. In the first hour after starting pain relief these parameters will be monitored with intervals of no longer than 15 minutes, after that with intervals of no longer than 1 hour. Maternal pulse oxymetry will also be monitored continuously.

Fetal heart rate and uterine activity will be measured continuously by external monitoring. When data are difficult to interpret or complications (such as meconium stained amniotic fluid, failure to progress in labor) occur, invasive monitoring by means of scalp electrode and intra-uterine pressure recording can be instituted.

Observations for known side effects will be made; respiratory depression, hypotension, nausea/vomiting and itching. Side effects will be managed by established local protocols.

Hypotension (systolic blood pressure < 90 mmHg or > 25% below baseline) will be treated with intravenous fluids, ephedrine 5 mg i.v. or phenylephrine 0.1 mg i.v. When oxygen saturation drops below 92% oxygen will be given.

Maternal pain score and pain appreciation score will be assessed using a visual analogue scale (VAS) ranging from 0-10. Women will be asked to mark the level of pain experienced during a contraction every hour starting at admission in the delivery room. Pain appreciation scores will be asked every hour, participating women will be asked to mark their level of satisfaction with analgesia. This will also be assessed using the visual analogue scale ranging from 0-10. After delivery an overall satisfaction score with pain(0-10) will be asked. Patient satisfaction will also be assessed by HADS and WDQ.

At delivery neonatal outcome including Apgar scores and cord blood gas analysis will be documented.

For economical analysis volumes of hospital care are measured prospectively alongside the clinical study in all participating centers as part of the case record form. Health resource use outside the hospital will be recorded by questionnaires filled out by the patients.

## Withdrawal of individual subjects

Subjects can leave the study at any time for any reason if they wish to do so without any consequences. The investigator can decide to withdraw a subject from the study for urgent medical reasons.

## Follow up of withdrawn subjects

Analysis will be done according to intention to treat.

# SAFETY REPORTING

## Section 10 WMO event

In accordance to section 10, subsection 1, of the WMO, the investigator will inform the subjects and the reviewing accredited METC if anything occurs, on the basis of which it appears that the disadvantages of participation may be significantly greater than was foreseen in the research proposal. The study will be suspended pending further review by the accredited METC, except insofar as suspension would jeopardise the subjects’ health. The investigator will take care that all subjects are kept informed.

## Adverse and serious adverse events

Adverse events are defined as any undesirable experience occurring to a subject during the study, whether or not considered related to the investigational product / the experimental treatment. All adverse events reported spontaneously by the subject or observed by the investiga­tor or his staff will be recorded.

A serious adverse event is any untoward medical occurrence or effect that at any dose:

- results in death;
- is life threatening (at the time of the event);

- requires hospitalisation or prolongation of existing inpatients’ hospitalisation;

- results in persistent or significant disability or incapacity;

- is a new event of the trial likely to affect the safety of the subjects, such as an unexpected outcome of an adverse reaction, lack of efficacy of an IMP used for the treatment of a life threatening disease, major safety finding from a newly completed animal study, etc.

- Serious adverse events that were defined for this study are respiratory failure requiring manual of assisted ventilation, CPR, anaphylactic shock, meningitis and epidural hematoma.

All SAEs will be reported to the accredited METC that approved the protocol, within 15 days after the sponsor has first knowledge of the serious adverse reactions.

SAEs that result in death or are life threatening should be reported expedited. The expedited reporting will occur not later than 7 days after the responsible investigator has first knowledge of the adverse reaction. This is for a preliminary report with another 8 days for completion of the report.

### Suspected unexpected serious adverse reactions (SUSAR)

Adverse reactions are all untoward and unintended responses to an investigational product related to any dose administered.

Unexpected adverse reactions are adverse reactions, of which the nature, or severity, is not consistent with the applicable product information (e.g. Investigator’s Brochure for an unapproved IMP or Summary of Product Characteristics (SPC) for an authorised medicinal product).

The sponsor will report expedited the following SUSARs to the METC:

- SUSARs that have arisen in the clinical trial that was assessed by the METC;

The remaining SUSARs are recorded in an overview list (line-listing) that will be submitted once every half year to the METC. This line-listing provides an overview of all SUSARs from the study medicine, accompanied by a brief report highlighting the main points of concern.

The expedited reporting of SUSARs through the web portal ToetsingOnline is sufficient as notification to the competent authority.

The sponsor will report expedited all SUSARs to the competent authorities in other Member States, according to the requirements of the Member States.

The expedited reporting will occur not later than 15 days after the sponsor has first knowledge of the adverse reactions. For fatal or life threatening cases the term will be maximal 7 days for a preliminary report with another 8 days for completion of the report.

### Annual safety report

In addition to the expedited reporting of SUSARs, the sponsor will submit, once a year throughout the clinical trial, a safety report to the accredited METC, competent authority, Medicine Evaluation Board and competent authorities of the concerned Member States.

This safety report consists of:

- a list of all suspected (unexpected or expected) serious adverse reactions, along with an aggregated summary table of all reported serious adverse reactions, ordered by organ system, per study;
- A report concerning the safety of the subjects, consisting of a complete safety analysis and an evaluation of the balance between the efficacy and the harmfulness of the medicine under investigation.

